**Fig. 2 Fig2:**
[figure not shown]
Enrolment schedule, treatment, and outcome measures. CSBM complete spontaneous bowel movement, SBM spontaneous bowel movement

### Statistical analysis

The analysis of the primary outcome will be based on both a full analysis (intention-to-treat analysis) and per-protocol sets (per-protocol analysis). The analyses of secondary outcomes will be based on the per-protocol sets. The full analysis set refer to the participants who are randomized and receive at least one treatment session. Any missing data will be replaced by the last measured value. The per-protocol sets will be defined as the participants who receive all treatment sessions and completed the study according to the protocol.

The statistical analysis will be performed by a statistician who is blinded to participant group allocation and will not be involved in other aspects of the study. The SPSS statistical package (version 18.0, International Business Machines Corporation, China) will be used to analyze the data. All data will be kept in duplicate by specific researchers. The results of the quantitative data analyses will be presented as means ± standard deviation. The Kolmogorov–Smirnov test will be applied as the normality test for quantitative variables. The Wilcoxon test or analysis of variance (ANOVA) will be used to compare the difference between groups according to the results of the Kolmogorov–Smirnov test. The results for categorical data will be compared with the chi-squared test and presented as a percentage. The statistical significance level will be set at 0.05 (two-sided) with a 95% confidence interval.

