#### Acupuncture group

All the study acupuncturists will be registered practitioners of traditional Chinese medicine with at least 5 years’ clinical experience, as well as a medical education background. The acupuncture treatments and manipulations will be standardized among acupuncture practitioners through live and recorded training. Outpatients will receive treatment in clinics and inpatients will be treated in wards. If inpatients are discharged, they will receive acupuncture in clinics by the same acupuncture practitioner. Sterile needles (size 0.30 × 40 mm and 0.35 × 75 mm; Guizhou Ande Medication Appliance, Ltd., Guiyang City, Guizhou Province, China) will be used.

For the acupuncture, we will use Wang’s classical 10 acupoints formula. These acupoints have been selected and combined for gastrointestinal disease after a stroke based on the clinical experience of an accomplished Chinese acupuncturist, Leting Wang, in the 1960s [26, 27]. The 10 acupoints include CV13 (*shangwan*), CV12 (*zhongwan*), CV10 (*xiawan*), bilateral ST25 (*tianshu*), CV6 (*qihai*), bilateral PC6 (*neiguan*), and bilateral ST36 (*zusanli*). All of the acupoints will be located according to the World Health Organization Standardized Acupuncture Points Location [28]. After sterilizing the skin, needles will be slowly and vertically inserted into ST25 (*tianshu*) bilaterally, without any manipulation. Needle insertion will stop upon piercing of the muscle layer of the abdominal wall (nearly 20 to 60 mm subcutaneously). Known side effects of needle insertion include mild soreness. Other needles will be inserted to a depth of 10–25 mm to predetermined acupoints and manually manipulated by rotation to produce the characteristic sensation of *deqi*. The *deqi* sensation is also called *needle sensation*, and refers to perceived subcutaneous tension around the needle, which is felt by the acupuncture practitioner, and soreness, numbness, distension, and heaviness around the acupuncture point that is felt by the participant. Each session will last for approximately 30 min. All needles will be removed with sterile cotton balls to avoid bleeding.

Each participant will be treated once a day and will receive 16 treatment sessions in total over 4 consecutive weeks. Treatment will be conducted 5 times per week in the first 2 weeks and 3 times per week in the last 2 weeks.

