#### Medication group

Participants in the medication group will receive 5 mg of mosapride citrate, 3 times per day for 4 consecutive weeks. Unused tablets will be collected by the researchers at the end of the treatment period.

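### All four secondary efficacy outcomes are analysed only in a per-protocol set that demands every treatment session, so none of them is compared between the groups as randomised

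*Protocol article*

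**What the plan says.** The Statistical analysis section of the protocol article names two analysis sets. The primary outcome is to be analysed in both. The secondary outcomes are assigned to one: "The analyses of secondary outcomes will be based on the per-protocol sets". No other set is named for them.

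The two sets are defined as follows:

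- Full analysis set: "The full analysis set refer to the participants who are randomized and receive at least one treatment session".
- Per-protocol set: "The per-protocol sets will be defined as the participants who receive all treatment sessions and completed the study according to the protocol".

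The Intervention section shows what a session could mean in each arm:

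- Acupuncture: each participant "will receive 16 treatment sessions in total over 4 consecutive weeks".
- Medication: "5 mg of mosapride citrate, 3 times per day for 4 consecutive weeks". No sessions are described.
- Control: routine care and secondary prevention only. No sessions are described.

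The efficacy outcomes affected, listed under Secondary outcome measures, are spontaneous bowel movements, stool consistency, straining and weekly laxative use. Adverse-event incidence is divided by the sample size of each group and is not affected.

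**The concern.** Whether a patient attends every session is known only after randomisation, and it can depend on the treatment and on how the patient is doing. The Discussion section states that neither therapists nor participants can be blinded, so a decision to skip or stop can also depend on knowing the allocation. Restricting an analysis to full attenders gives up the protection of randomisation.

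The restriction also falls unequally. One missed acupuncture session removes a patient, whereas no control can be removed for that reason. If the missed sessions are related to outcome, the acupuncture patients who remain differ from the controls for reasons other than treatment.

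With no full-set analysis planned for these outcomes, a reader of the results could not see whether this had happened. The choice also sits badly with the article's description of the design as pragmatic, and with its aim of informing later trials about effect sizes and the completeness of the data.

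**Working it through.** **Step 1. The article's own figures.** The schedule is "Treatment will be conducted 5 times per week in the first 2 weeks and 3 times per week in the last 2 weeks". This gives 5 × 2 + 3 × 2 = 16 sessions, which agrees with the stated total. Each arm has 40 patients (3 × 40 = 120, also as stated). The article gives no attendance rate, dropout rate or standard deviation, so everything in steps 3 to 5 rests on assumed inputs.

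**Step 2. What each condition of the per-protocol set can exclude.**

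| Arm | All sessions received | Completed according to the protocol |
|---|---|---|
| Acupuncture | Excludes anyone with fewer than 16 of 16 | Can exclude |
| Medication | Not defined: tablets, no sessions | Can exclude |
| Control | Cannot exclude: no sessions | Can exclude |

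**Step 3. Patients left in the acupuncture arm.** Assume that each session is attended independently with probability p. The fraction meeting the session condition is q = p^16, and the expected number is 40q.

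**Step 4. Shift in the acupuncture mean with no true effect.** Let the outcome have SD 1, and let a latent adherence score correlate ρ with it. Keep the most adherent fraction q of the acupuncture arm and apply no such filter to control. With c = z(1 − q) and λ = φ(c)/q:

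- shift in mean = ρλ
- remaining variance = 1 − ρ²λ(λ − c)

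| p (assumed) | q = p^16 | Left of 40 | λ | Shift, ρ = 0.2 | Shift, ρ = 0.3 | Shift, ρ = 0.5 |
|---|---|---|---|---|---|---|
| 0.99 | 0.851 | 34 | 0.272 | 0.05 SD | 0.08 SD | 0.14 SD |
| 0.98 | 0.724 | 29 | 0.462 | 0.09 SD | 0.14 SD | 0.23 SD |
| 0.95 | 0.440 | 18 | 0.896 | 0.18 SD | 0.27 SD | 0.45 SD |
| 0.90 | 0.185 | 7 | 1.442 | 0.29 SD | 0.43 SD | 0.72 SD |

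For p = 0.98, c = −0.594 and φ(c) = 0.334, so λ = 0.334/0.724 = 0.462 and the shift at ρ = 0.3 is 0.3 × 0.462 = 0.14 SD. The sign follows the sign of ρ. It is positive if better responders attend more, and negative if early responders stop coming.

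The effect on the SD is small. At ρ = 0.3 the variance factor is 1 − 0.09 × 0.462 × (0.462 + 0.594) = 0.956 for p = 0.98. For p = 0.95 it is 1 − 0.09 × 0.896 × (0.896 − 0.151) = 0.940. The SD therefore falls by about 2% and 3%.

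**Step 5. Consequence for a test at two-sided 0.05.** This uses a normal approximation, no true effect, ρ = 0.3, 40 controls and 40q acupuncture patients. The rejection rate is 7.3% with 80% of the acupuncture arm retained, 9.4% with 70% and 14.5% with 50%, against a nominal 5%. Precision also falls. For an assumed true difference of 0.5 SD, power is 60.9% with 40 against 40 and 52.8% with 28 against 40.

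**The case against.** The best case for leaving the plan alone is that little depends on these outcomes. This is a pilot whose size was set for practical reasons, and the primary outcome already has a full-set analysis. Spontaneous bowel movements are calculated in the same way as the primary outcome and are closely related to it. That stands, and it limits the severity.

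Four stronger readings are tempting, and the article does not support them.

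- *The rule inflates the active-arm effect.* This holds only if poor responders are the ones who miss sessions. If early responders stop, the bias reverses. Sessions missed for reasons unrelated to bowel function need cause no bias. The article does not say why sessions might be missed.
- *Control keeps all 40 patients.* It loses nobody through the session condition, but controls who do not complete according to the protocol are excluded too.
- *Tablet non-adherers are removed as well.* Nothing in the article requires every tablet to be taken. If each intake were counted as a session, there would be 3 × 28 = 84, and 99% adherence per intake would leave 0.99^84 = 0.43, about 17 of 40. That reading is a possibility, not the stated rule.
- *The rule spoils the SDs and effect sizes needed to plan the main trial.* The effect on the SD is about 2 to 3% at the two main attendance assumptions. The article does not say that the main trial will be sized on a secondary outcome, and a full-set estimate of the primary outcome will exist.

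The illustration can also be criticised. Independent attendance with a common p sits awkwardly with a stable patient-level adherence score. If missed sessions cluster in a few patients, more patients complete all 16 at the same average attendance, so the retention figures lean pessimistic. Treating inpatients on the ward may also keep attendance high.

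It cannot be said that the matter is simply left to a statistical analysis plan. The article states both the set and its definition, and treats the primary outcome differently in the same paragraph.

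**Conclusion.** The concern holds in a limited form. As written, no secondary efficacy outcome is analysed by randomised group, and the filter applied is strict for acupuncture, undefined for medication and, as regards sessions, empty for control. The resulting comparisons may be biased in a direction that cannot be known in advance.

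The size depends on attendance and on its correlation with outcome, neither of which the article gives. At attendance of 0.98 to 0.95 per session and a correlation of 0.3, about 29 to 18 of 40 acupuncture patients remain and the spurious shift is about 0.14 to 0.27 SD. At 0.99 it is under 0.1 SD. Only the exclusion of acupuncture patients is certain from the text.

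This should be fixed, but it does not undermine the trial, because this sentence leaves the primary outcome's full-set analysis in place and the study is a pilot.

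**What to change.** Replace the sentence on secondary outcomes with wording such as: *Secondary outcomes, like the primary outcome, will be analysed in the full analysis set, with participants in the group to which they were randomised. The per-protocol analysis is a sensitivity analysis only.*

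Redefine the per-protocol set so that it can be applied in each arm: a stated adherence criterion for acupuncture, a corresponding one for tablets, and protocol violations and completion requirements that apply to control as well. The full-set definition also refers to receiving a session, so the same revision should say how it is read for medication and control.

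The cost is a change of wording and one more analysis run. All participants are already asked to keep the defecation diary for 8 weeks, so no new data collection is needed. There are two downsides. The secondary estimates may look less favourable. Participants who withdraw will also have missing diary data, which the article would fill with the last measured value. That rule can introduce bias of its own, so the handling of missing data for these outcomes needs to be settled at the same time.

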#### Control group

Participants in the control group will receive routine health care and secondary prevention treatments for ischemic stroke. For participants with no SBMs over 4 or more consecutive days, cathartic treatment will be given. Details related to the usage of cathartic drugs will be recorded during the trial.

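### Both analysis sets are defined by treatment sessions, which only the acupuncture arm has, so the set labelled intention-to-treat is not one and the per-protocol session rule has no clear meaning in the other two arms

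*Protocol article*

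**What the plan says.** The Statistical analysis section of the protocol article names two sets for the primary outcome: "The analysis of the primary outcome will be based on both a full analysis (intention-to-treat analysis) and per-protocol sets (per-protocol analysis"). It then defines them. For the first: "The full analysis set refer to the participants who are randomized and receive at least one treatment session". For the second: "The per-protocol sets will be defined as the participants who receive all treatment sessions and completed the study according to the protocol". Secondary outcomes use the second set alone: "The analyses of secondary outcomes will be based on the per-protocol sets".

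The intervention sections describe three different kinds of exposure. In the Acupuncture group section, participants "will receive 16 treatment sessions in total over 4 consecutive weeks". The Medication group section gives mosapride tablets three times daily for 4 weeks, with unused tablets collected at the end. The Control group section has no sessions: "Participants in the control group will receive routine health care and secondary prevention treatments for ischemic stroke".

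The Discussion states that participants and therapists cannot be blinded. Under Randomization and allocation concealment, the envelope is opened once baseline measurements are complete.

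**The concern.** An intention-to-treat set keeps every randomised participant in the allocated arm whether or not treatment started. Here the set with that label has an exposure condition, expressed in a unit that exists in one arm of three.

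Participants learn their arm when the envelope is opened, so the decision not to start, or to miss visits, can depend on the arm. A rule that removes participants after that point in some arms and not in others can select on prognosis or motivation. This would happen inside the analysis meant to protect the randomised comparison. The trial is meant to supply effect sizes and variability for later trials, so a distorted estimate would carry into their design.

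**Working it through.** **1. The plan's own count.** The Acupuncture group section says: "Treatment will be conducted 5 times per week in the first 2 weeks and 3 times per week in the last 2 weeks". That gives 5 × 2 + 3 × 2 = 16 sessions, matching the stated 16. The medication regimen is 3 × 7 × 4 = 84 intakes. The sample is 3 × 40 = 120.

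**2. Who is in the full analysis set (acupuncture / medication / control)?**

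| Reading | Membership |
|---|---|
| Literal: a session is needed | at most 40 / 0 / 0 |
| Lenient: the rule applies only where there is something to start | 40 − k / 40 − m / 40 |
| All randomised, as allocated | 40 / 40 / 40 |

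Here k is the number of acupuncture participants lost before session 1. The number of medication participants lost before a first dose is m, if a first dose is taken to count (otherwise m = 0). The document gives neither number.

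**3. Size in the full set.** One non-starter is 1/40 = 2.5% of an arm. If a share f of an arm is removed and those removed differ from the rest by d standard deviations (SD), the arm mean moves by f × d. With d = 0.5 (assumed), one non-starter moves it by 0.025 × 0.5 = 0.0125 SD. The standard error of a 40 versus 40 difference is √(2/40) = 0.224 SD. A few non-starters therefore matter little.

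**4. Size in the per-protocol set.** The document gives no attendance rate. Suppose each session is attended independently with probability p. The chance of attending all 16 is p^16:

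| p (assumed) | p^16 | of 40 |
|---|---|---|
| 0.99 | 0.851 | about 34 |
| 0.98 | 0.724 | about 29 |
| 0.95 | 0.440 | about 18 |
| 0.90 | 0.185 | about 7 |

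Independence is unlikely. If missed sessions cluster in a few people, more participants complete at the same mean attendance. In the extreme, 38 of 40 attend everything and 2 attend nothing; mean attendance is still 95%, and 38/40 = 95% complete all 16. So at 95% attendance the share runs from 44% under independence to 95% under complete clustering.

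If 10% to 50% of one arm is removed and those removed differ by 0.5 SD, that arm's mean shifts by 0.05 to 0.25 SD. The upper end is about one standard error.

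**5. The medication arm.** If full receipt means all 84 intakes, p^84 at p = 0.99, 0.98 and 0.95 is 0.430, 0.183 and 0.013, or about 17, 7 and 0.5 of 40. If it means something looser, nearly all may qualify. The wording does not settle which.

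**The case against.** The fair reply is that the word session is loose drafting. The Study design section describes all three groups as receiving 4 weeks of continuous treatment, so the likely intent is that participants started, or completed, their allocated regimen. An exposure-based full set is common. Allocation follows consent and a one-week baseline diary, and some participants are treated on the ward, so few may fail to start. The trial is a pilot, with numbers set for practical reasons. Every per-protocol set departs from randomisation, and for the primary outcome both sets are reported.

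Much of this stands. The literal reading is probably not intended, the full-set effect is probably small, and using a per-protocol set is not in itself an error. But the charitable reading still puts an exposure condition in a set called intention-to-treat, and controls receiving routine care cannot fail it. This is a rule the article states, not a detail it leaves to another document. A numeric tablet cut-off could be left to an analysis plan and is not the complaint.

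A reader might go further and infer that the per-protocol rule asks nothing of controls, that all 40 qualify automatically, and that at 95% attendance the comparison becomes 18 against 40. The document does not support this. The definition has a second condition, completion of the study according to the protocol, which applies to controls too. Their number is unknown, and the 18 itself rests on an assumed attendance rate and independence.

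**Conclusion.** The point holds. The session wording either empties two arms or permits exclusions after randomisation that depend on the arm, in a trial whose participants know their allocation. The set labelled intention-to-treat is therefore not one.

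The likely distortion of the primary full-set result is small if nearly everyone starts. The per-protocol set is the more exposed: its session criterion is much stricter for acupuncture than for control, and the secondary outcomes have no full-set analysis behind them. How strict it proves depends on attendance, which the document does not give; the retention and bias figures are ranges under stated assumptions, not forecasts.

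**What to change.** - **Full analysis set:** all randomised participants, analysed in the arm allocated. Name it as the set that decides the superiority comparison with routine care.
- **Per-protocol set:** give each arm an adherence criterion it can meet or fail. Use sessions attended for acupuncture and returned-tablet count for medication. For control, use completion of the study and diary without acupuncture or mosapride. Fix the threshold before outcomes are seen; the document supplies no value.
- **Role of each set:** treat per-protocol as supportive for superiority. The Background also hypothesises that acupuncture is no less effective than mosapride; for that comparison, report per-protocol alongside the full set rather than demoting it to a sensitivity analysis.

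The cost is a few sentences. Diaries and tablet returns are already collected, and session attendance should be on record. Adherence records reveal the arm, so someone other than the blinded statistician should derive the per-protocol flag.

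There is one small downside. Non-starters with no diary after baseline would enter the full set, and the current last-value rule would carry their baseline forward and give them zero change. A missing-data approach for them needs to be stated.

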#### Follow-up

After the 4-week treatment, all participants will enter an additional 4-week follow-up period. During this time, they will receive routine health care and secondary prevention as provided to all other patients with ischemic stroke. Laxatives will be allowed for use as emergency drugs during the follow-up period. However, acupuncture treatment and mosapride citrate are not permitted during follow-up.

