### Outcome measures

#### Primary outcome measure

The primary outcome measure will be the change in the weekly mean number of CSBMs over the 4 weeks of the intervention and the 4 weeks of the follow-up. A CSBM is defined as a SBM unrelated to the administration of laxatives or finger manipulation, accompanied by a self-reported feeling of complete evacuation. Bowel movements achieved with the help of glycerin, enemas, or finger manipulation are not considered spontaneous. If bowel movements occur within 24 h after the intake of laxatives, they will not be considered spontaneous. However, if bowel movements occur more than 24 h after administration of laxatives, they will be considered spontaneous. The total number of CSBMs during the treatment period and follow-up period will be averaged to obtain mean weekly CSBMs.

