## Discussion

Constipation is a common health problem after an ischemic stroke. Relevant research has indicated that constipation after an ischemic stroke can impair the removal of metabolic waste [29], aggravate the development of atherosclerosis, increase the risk of cerebral vasospasm and neural damage, lead to the detachment of deep vein thrombosis and cause thromboembolism, and induce the recurrence of cardiovascular and cerebrovascular diseases [7, 8]. Constipation may severely impair a patient’s rehabilitation and their quality of life. The results of this study will provide preliminary data on the safety, tolerability, and preliminary effectiveness of acupuncture for constipation symptoms after stroke. It will provide evidence for sample size calculations of subsequent large-scale multi-center randomized controlled trials by assessing effect sizes, variability, and the completeness of the data. The study will be a preliminary investigation into the potential enhancement of a currently used intervention and may contribute to changes in future clinical practice.

Acupuncture is popular in China due to its long history, simple administration, therapeutic effects, low cost, and relative safety. It is also increasingly practiced and requested by patients in Western countries as a complementary and alternative medicine [30]. The World Health Organization has drawn up a provisional list of diseases that could potentially be treated with acupuncture, including constipation, stroke, and its sequelae [31, 32]. To treat constipation, we will use Wang’s classical 10 acupoints. These 10 points are combined to treat gastrointestinal disease after a stroke and are based on acupuncture theory and decades of clinical experience [33, 34]. These points were selected because: (1) all 10 acupuncture points have been used for thousands of years in traditional Chinese medicine to treat constipation and other gastrointestinal diseases and (2) from the perspective of evidence-based medicine, clinical randomized controlled trials and systematic reviews also show that these acupuncture points, individually or in combination, may be an effective treatment for constipation [21, 35–38].

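### Carrying the last value forward can put on-treatment or baseline bowel counts into the full-analysis-set primary analysis and distort the effect size and SD this pilot is meant to supply

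*Protocol article*

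**What the plan says.** The Statistical analysis section gives one rule for incomplete data: "Any missing data will be replaced by the last measured value". It names no alternative and no sensitivity analysis aimed at missing data.

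The primary outcome is analysed in two sets. In the first, "The full analysis set refer to the participants who are randomized and receive at least one treatment session". The second is limited to "participants who receive all treatment sessions and completed the study according to the protocol". For the other outcomes, "The analyses of secondary outcomes will be based on the per-protocol sets".

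The Primary outcome measure section defines the endpoint as "the change in the weekly mean number of CSBMs over the 4 weeks of the intervention and the 4 weeks of the follow-up". Under Study design, outcomes are assessed at baseline, week 4 and week 8 from a diary that runs throughout. The Follow-up section says that "acupuncture treatment and mosapride citrate are not permitted during follow-up", so the second half of the primary outcome is measured off trial treatment.

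The Discussion states the pilot's purpose as evidence for "sample size calculations of subsequent large-scale multi-center randomized controlled trials by assessing effect sizes, variability, and the completeness of the data".

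**The concern.** Carry-forward assumes that a participant's bowel function stays where it was last recorded. This design makes that doubtful in two places.

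- **After week 4.** The trial treatments stop. A value recorded under acupuncture or mosapride is entered for a period in which neither is given. If benefit fades, the filled value shows benefit that may no longer exist.
- **Before week 4.** The full analysis set keeps anyone who had one session. A participant with no later value is given baseline, a change of exactly zero.

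The filled values then enter the ANOVA or Wilcoxon comparison as if observed. Loss could well differ by arm: the Discussion says participants are not blinded, and the acupuncture arm attends 16 sessions while the control arm receives routine care only. The pilot is meant to pass effect sizes and variability to a larger trial, so a distortion in either carries into that trial's sample size.

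**Working it through.** **The plan's own figure.** 3 × 40 = 120 is consistent. The Sample size section sets it on practical grounds, with no effect size, SD, power or dropout rate. There is nothing to recompute, and carry-forward does not affect it.

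**Inputs from the document.** Assessments at baseline, week 4 and week 8; treatment in weeks 1–4 only; carry-forward for any missing value; two-sided α of 0.05.

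**Assumed inputs, not in the document.** SD of change s = 1.5 CSBM per week; missing fraction q of 10% to 30%; loss unrelated to outcome within arm; 80% power for the later trial. Unless stated otherwise, mean changes at week 4 are 1.5 (acupuncture) and 0.5 (comparator), a contrast d4 = 1.0. The comparator stays at 0.5 at week 8.

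**1. Week-4 value carried to week 8, equal loss.** Reported contrast = (1 − q)·d8 + q·d4.

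| True d8 | q = 10% | q = 20% | q = 30% |
|---|---|---|---|
| 0.50 | 0.55 | 0.60 | 0.65 |
| 0.25 | 0.325 | 0.40 | 0.475 |
| 0 | 0.10 | 0.20 | 0.30 |

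If d8 = d4 = 1.0, the formula returns 1.0 for every q, so there is no bias.

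**2. Baseline carried to week 4.** Reported contrast = (1 − qA)·1.5 − (1 − qC)·0.5, where A is acupuncture and C the comparator.

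- Equal loss of 10%, 20% or 30%: 0.90, 0.80 or 0.70.
- 5% in acupuncture, 20% in comparator: 0.95 × 1.5 − 0.80 × 0.5 = 1.025.
- 20% in acupuncture, 5% in comparator: 0.80 × 1.5 − 0.95 × 0.5 = 0.725.

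**3. SD.** After zero-filling, the variance in an arm with mean change μ is (1 − q)s² + q(1 − q)μ². This is below s² only when (1 − q)μ² < s². At q = 20%:

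- Changes 1.5 and 0.5: variances 2.16 and 1.84, average 2.00, SD 1.41 (down from 1.50).
- Changes 2.5 and 1.5: variances 2.80 and 2.16, average 2.48, SD 1.57 (up from 1.50).

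Carrying week 4 to week 8, with equal SDs in the two periods, adds q(1 − q)(μ4 − μ8)². That term cannot be negative. With acupuncture falling from 1.5 to 0.75 and q = 20%, the pooled SD goes from 1.50 to about 1.52.

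**4. Effect on a later trial's n per arm.** n = 2(1.96 + 0.84)²·SD²/d², using unrounded normal quantiles.

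- Week 4, equal 20%: 36 becomes 50. Unequal loss gives 31 (5% v 20%) or 65 (20% v 5%).
- Week 8, true 0.50, equal 20%: 142 becomes 99.
- Week 8, true 0.25, equal 20%: 566 becomes 226.

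**5. Both paths together.** Take 10% lost before week 4 and 10% of the remainder lost after it, with true contrasts 1.0 and 0.25. The week-8 result is 0.81 × 0.25 + 0.09 × 1.0 + 0.10 × 0 = 0.29. A simulation agreed: 0.29 against 0.24 with complete data. At week 4 it gave 0.89 against 0.99. The SD fell from 1.50 to 1.46 at week 4 and to 1.45 at week 8. The zero-fills partly offset the upward pull at week 8.

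**6. What counts as the last measured value.** The article does not say whether it is an assessment value or a diary week.

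- By assessment: anyone without a week-4 value gets baseline, and anyone with a week-4 but no week-8 value gets the on-treatment value.
- By diary week: baseline reaches week 4 only for someone with no post-baseline diary, and the on-treatment value fills weeks 5–8 for someone with no follow-up diary.

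The on-treatment path exists on both readings.

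**The case against.** The strongest case on the other side has four parts.

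- **Scope.** The per-protocol set requires completion, so it leaves little to fill. The primary outcome is also analysed there, and secondary outcomes only there. This stands: the problem lies mainly in one analysis of one outcome. The per-protocol analysis does not cure it, because dropping non-completers gives a differently selected estimate and does not test the missing-data assumption.
- **Baseline path.** The diary gives weekly data, so a participant lost in week 3 may carry week 2 and not baseline. This stands, and that path is conditional on how the rule is read.
- **No certain bias.** If few data are missing, or the contrast persists after treatment stops, the week-8 bias is small or nil. This also stands. The document gives no dropout rate.
- **Direction.** A reader might infer that carry-forward always makes the SD and standard errors too small, and hence the next trial too small. The documents do not support that. Working step 3 shows that the SD can rise. With one value per participant, the usual standard error is valid for the mean of the filled variable; the trouble is that this mean is the wrong target. Even in the limiting case of mean change near zero, where 20% zero-filling multiplies the variance by 0.80, the contrast is multiplied by 0.80 as well. Then n scales by 0.80/0.64 = 1.25, about 25% too large. A trial 20% too small would follow only if the next trial took this pilot's SD but its effect from elsewhere.

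What survives is that a stated rule can enter an on-treatment value for an off-treatment period in the primary analysis. This is a choice the article makes outright, not detail left to a fuller document.

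**Conclusion.** The point holds for the full-analysis-set analysis of the primary outcome. Carry-forward pulls the week-8 contrast toward the week-4 contrast when participants are lost after treatment ends, and it dilutes the week-4 contrast, or shifts it either way, where baseline is carried. Under the illustrative inputs, 20% loss moves a week-8 contrast by 0.1 to 0.2 CSBM per week when the true value is 0.5 to 0, and takes 0.2 off a week-4 contrast of 1.0.

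No single direction can be claimed for the SD or for the next trial's sample size. The size of the effect depends on the amount, timing and balance of missing data, and on how far benefit fades, none of which the document gives. The planned 120 is not in question. The change should be made because it is cheap and protects two of the quantities the pilot is meant to deliver.

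**What to change.** For the full-analysis-set analysis of the primary outcome, replace carry-forward with one of the following:

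- a mixed model for repeated measures on the diary data, with arm, period (treatment, follow-up), arm-by-period and baseline, reporting the contrast for each period; or
- multiple imputation carried out separately by arm.

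In either case, use each participant's observed diary weeks and do not fill gaps with the last value. Both methods rest on data being missing at random given what was observed, and the text should say so. Keep carry-forward only as a labelled sensitivity analysis, and state there whether the carried value is an assessment or a diary week. The definition of the full analysis set can stay as it is for this purpose.

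The cost is a few sentences, slightly more analysis work and slightly wider confidence intervals. The diary data are already collected, the stated package (SPSS) fits mixed models, and nothing changes in recruitment, treatment or visits.
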